**Figure 3 F3:**
[figure not shown]
**Measurement of plantar flexion strength of the toe-flexors of the hallux. Participant positioning (A) and recording of forces produced under the hallux (B)**.

##### (vi) Plantar pressure measurement

Plantar pressures will be recorded during level barefoot walking using the MatScan^® ^system (Tekscan^®^, Boston, MA, USA). The two-step gait initiation protocol will be used to obtain foot pressure data, as it requires fewer trials than the mid-gait protocol and has similar re-test reliability [32]. Three trials will be recorded, which has been found to be sufficient to ensure adequate reliability of pressure data [32,33]. Following data collection, the Research Foot^® ^software (version 5.24) will be used to construct individual "masks" to determine maximum force (kg) and peak pressure (kg/cm^2^) under seven regions of the foot: hallux, lesser toes, 1^st ^MPJ, 2^nd ^MPJ, 3^rd ^to 5^th ^MPJs, midfoot and heel (Figure 4a). For each region, the median of the three trials will be used for analysis. Typical plantar pressure recordings from a participant are shown in Figure 4b.

**Figure 4 F4:**
[figure not shown]
**The seven masked regions used for plantar pressure analysis (A) and typical plantar pressure recordings from a participant (B)**.

##### (vi) Global satisfaction with the treatment

Global satisfaction with the treatment will be assessed using a 5-point Likert scale, as well as a dichotomous (yes/no) scale. The five point-Likert scale will ask "How satisfied are you with the treatment you received for your big-toe joint pain?", and will have the following five responses: "Dissatisfied", "Only moderately satisfied", "Fairly satisfied", "Clearly satisfied" and "Very satisfied". The dichotomous scale of satisfaction will be answered as "Yes"' or "No" in response to the question: "Would you recommend the treatment that you received to someone else with big-toe joint pain".

##### (vii) Health related quality of life

The Short-Form-36 (version two) (SF-36) questionnaire will be used to assess health related quality of life. The SF-36 is a 36 question survey that measures eight health concepts most affected by disease and treatment. The eight health concepts can then be used to form two summary measures: *Physical health *and *Mental health*. The Short Form-36 (SF-36) has been extensively validated and is one of the most widely used instruments to measure health status. The SF-36 shows content, concurrent, criterion, construct, and predictive evidence of validity. The reliability of the eight concepts and two summary measures has been assessed using both internal consistency and test-retest methods. Reliability statistics have exceeded 0.80 [34-37].

##### (viii) Self-reported magnitude of symptom change

Self-reported magnitude of symptom change will be measured using a 15-point Likert scale. The scale will ask participants "how much have your symptoms in your big-toe joint have changed from the beginning of the study to now?". The fifteen responses will range from "A very great deal better" to "A very great deal worse".

##### (ix) Use of rescue medications to relieve pain at the first metatarsophalangeal joint

The number of participants who consumed rescue medication (e.g., paracetamol) and mean consumption of rescue medication to relieve pain at the first MPJ (mean grams of paracetamol/participant/month] will be assessed using a medications diary that participants will self-complete [38,39]. The diary will be returned to the assessor at monthly intervals for analysis.

##### (x) Frequency and severity of adverse events as safety variables

The frequency (number of participants affected and number of cases) and types of adverse events (including adverse drug reactions) in each treatment group during the trial will be recorded using a questionnaire that participants will complete during the follow-up appointments at 1, 3 and 6 months post-treatment [40]. To classify the 'type' of adverse event, a blinded assessor will classify the adverse event as being serious or non-serious [40]. Any serious adverse events, defined as adverse events leading to serious disability, hospital admission, or prolongation of hospitalisation, life-threatening events; or death) will be further classified using the International Classification of Diseases (ICD) codes [41]. Non-serious adverse events will include both local (pain, effusion and heat, with each classified as mild, moderate, severe) and systemic adverse events. An open-response type format will also be available for participant responses.

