### Intra-articular injections for the treatment groups

Participants will be randomised to receive a single intra-articular injection of up to 1 ml of hyaluronan (Synvisc^®^; Genzyme Biosurgery, Genzyme Corporation, NJ, USA) or sterile saline (placebo) into the first MPJ. Each 2 ml ampoule of Synvisc^® ^contains 16 mg of hylan G-F 20 (cross-linked hylan polymers; hylan A and B), 17 mg sodium chloride, 0.32 mg disodium hydrogen phosphate, 0.08 mg sodium dihydrogen phosphate monohydrate. The hyaluronan is extracted from chicken combs and the purified material has an average molecular weight of 6,000 kDa.

The injections will be performed by the same experienced interventional radiologist ([name]) using fluoroscopic imaging to ensure accurate deposition of the hyaluronan within the joint. As the Synvisc^® ^is provided in ampoules that are labelled with the product name, it will not be possible to blind the injector, however this person is not involved in generation of the allocation order, recruitment, assessment or data analysis. The intra-articular injection will be performed using a 21 gauge (0.80 × 19 mm) Surflo^® ^(Terumo^® ^Corp., Tokyo, Japan) winged infusion set under aseptic procedures. Either a dorso-lateral or dorso-medial approach for injection will be used at the discretion of the injector (depending on which approach provides minimum interference from the osteophytes at the first MPJ joint margins). No anaesthetic will be used. If the participant has bilateral painful first MPJs, only one side (the most painful side) will be treated and used for data collection. The injector will record the volume of the agent that is injected.

Participants will be given the option of a second and final intra-articular injection (of Synvisc^® ^or sterile saline according to the treatment group they are in) on days 30 or 90 if there is no improvement in pain (assessed using the VAPS for pain during walking or at rest) and the participant has not experienced severe adverse effects after the first injection).

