#### Primary outcome measures

Outcome measurements (primary and secondary) will occur at four time-points at baseline, 1, 3 and 6 months post-treatment (after the intra-articular injection of Synvisc^® ^or placebo). The assessor performing the measurements will be blinded as to which treatment group participants have been allocated to. Participants who receive a second treatment at day 30 or 90 will be followed for a further 30 days or 90 days respectively and undergo outcome measurements at 7 or 9 months respectively.

The primary outcome measures will be the *Pain *and *Function *subscales of the Foot Health Status Questionnaire (FHSQ) [24]. The FHSQ includes 13 questions that assess four domains of foot health, *Foot pain, Foot function, Footwear *and *General foot health*. The FHSQ has been subjected to an extensive validation (content, criterion and construct validity) process. It has a high test-retest reliability (intraclass correlation coefficients ranging from 0.74 to 0.92) and a high degree of internal consistency (Cronbach's α ranging from 0.85 to 0.88) [24]. Rigorous reviews have rated it as one of the highest quality foot health status measures currently available [25-27].

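### Adverse-event collection is not timed to the optional second injection, so local reactions to it are first asked about 60 or 90 days later

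*Protocol article*

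**What the plan says.** Four parts of the protocol article's Methods bear on this.

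- **Adverse events, secondary outcome (x).** Events are recorded with a questionnaire that participants "complete during the follow-up appointments at 1, 3 and 6 months post-treatment". What is recorded is "The frequency (number of participants affected and number of cases) and types of adverse events (including adverse drug reactions) in each treatment group" over the trial. Non-serious events include pain, effusion and heat at the joint, each graded for severity.
- **Intra-articular injections for the treatment groups.** A second injection is optional "on days 30 or 90 if there is no improvement in pain (assessed using the VAPS for pain during walking or at rest", provided that "the participant has not experienced severe adverse effects after the first injection".
- **Primary outcome measures.** Participants who have a second injection "will be followed for a further 30 days or 90 days respectively and undergo outcome measurements at 7 or 9 months respectively". The same section says that outcome measurements cover both primary and secondary outcomes.
- **Rescue medication, secondary outcome (ix).** Participants complete a medication diary themselves. "The diary will be returned to the assessor at monthly intervals for analysis". It is described for rescue medication only.

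No adverse-event form is linked to the date of a second injection, and no count by injection number or per injection is stated. The Discussion accepts that re-injection may complicate interpretation, without mentioning safety.

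**The concern.** Pain, effusion and heat after a joint injection are short-lived. Asking participants to remember and grade them two or three months later is a weaker measurement than asking after one month, so the two injections are not measured alike. The statistical analysis plan cannot repair this, because it concerns what is collected.

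The denominator raises a second question. Re-injection is triggered by lack of pain improvement, so the number of injections per participant could differ between arms. If it does, the number of cases per arm no longer reflects the risk per injection, which a clinician weighing one more injection would want to know.

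**Working it through.** **1. Recall gap.** Gap = day of the next scheduled adverse-event questionnaire minus day of injection, with months 1, 3 and 6 taken as days 30, 90 and 180.

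| Injection | Next questionnaire | Gap | Extra visit for the re-injected | Days from second injection to extra visit |
|---|---|---|---|---|
| First, day 0 | month 1 | 30 days | none | – |
| Second, day 30 | month 3 | 90 − 30 = 60 days | month 7 | 210 − 30 = 180 |
| Second, day 90 | month 6 | 180 − 90 = 90 days | month 9 | 270 − 90 = 180 |

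The extra visits come after the next regular questionnaire, so using the form there would not shorten the gap.

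**2. Dilution factor.** Let qA and qP be the reaction risks per injection on hyaluronan and placebo, and rA and rP the shares re-injected. Expected cases per arm = n × (1 + r) × q. With equal n:

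case ratio per arm = (qA/qP) × (1 + rA)/(1 + rP).

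If rA = rP, the factor is 1.

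**3. How far apart could rA and rP be?** The article gives no re-injection shares, so these are assumed. The Sample size section supplies a 14-point difference and an SD of 25 on the Foot Health Status Questionnaire (FHSQ) pain scale. Those inputs reproduce its figure: 2 × (1.960 + 1.282)² × 25²/14² = 67.0 per arm, and 67/0.95 = 70.5, which rounds up to the stated 71.

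For illustration, take 25 as the SD of change, treat no improvement as a change of zero or less, use FHSQ pain in place of the visual analogue trigger, and assume that everyone who qualifies accepts. With mean placebo improvement m, rP = Φ(−m/25) and rA = Φ(−(m + 14)/25).

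| m (assumed) | rA | rP | (1+rA)/(1+rP) |
|---|---|---|---|
| 0 | 0.288 | 0.500 | 0.86 |
| 5 | 0.224 | 0.421 | 0.86 |
| 10 | 0.169 | 0.345 | 0.87 |
| 15 | 0.123 | 0.274 | 0.88 |
| 20 | 0.087 | 0.212 | 0.90 |

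A wider assumed split of 20% and 50% gives 1.20/1.50 = 0.80. With no treatment effect, rA = rP at every m.

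**4. What that does to counts** (75 per arm; all risks assumed)

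- Small excess: 15% against 12% per injection, re-injection 20% and 50%. Cases are 75 × 1.20 × 0.15 = 13.5 and 75 × 1.50 × 0.12 = 13.5. A per-injection ratio of 1.25 appears as 1.00.
- Large excess: 21% against 10%, re-injection 17% and 34%. Cases are 75 × 1.17 × 0.21 = 18.4 and 75 × 1.34 × 0.10 = 10.05. A ratio of 2.10 appears as 1.83.

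**5. Recall and dilution together.** If only a share s of second-injection reactions is recalled, the factor becomes (1 + s·rA)/(1 + s·rP). Take 21% against 15% per injection (ratio 1.40) and re-injection of 22% and 42%:

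- s = 1: 1.40 × 1.22/1.42 = 1.20
- s = 0.5: 1.40 × 1.11/1.21 = 1.28
- s = 0: 1.40

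Forgetting second-injection reactions therefore reduces the dilution, at the price of losing those events.

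**The case against.** The strongest case on the other side has five parts.

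- **Unequal re-injection is not a fact of the plan.** A reader might infer that re-injection rates are bound to differ. The article does not say so, and with no effect on pain they are equal in expectation. This stands, and the dilution is conditional on an effect.
- **Counts per arm are legitimate.** Optional re-injection is a deliberate pragmatic feature, and events per randomised arm compare the two strategies without bias from selection. A reader might infer that such counts hide harm. They do not give the risk per injection, but they are not invalid, and a large excess stays visible. This stands.
- **A clean early comparison may already exist.** The questionnaire is completed at month 1, re-injection starts no earlier than day 30, and the Statistical analysis section analyses outcomes at 1, 3 and 6 months. On that reading the one-injection comparison is already collected and analysed. This largely stands, so the request is to report it explicitly.
- **The 7- and 9-month visits may already include adverse events**, since these are listed as a secondary outcome. The Primary outcome measures section can be read that way, but the adverse-event section names only 1, 3 and 6 months. A reader might infer that the form is definitely absent at the later visits. The text supports only that the two sections do not settle it.
- **The available risks are weak.** The article's 21% (3/14) is per participant after up to three injections of another hyaluronan product, and its 10% (2/20) also concerns that product. Neither gives a placebo risk. This stands, so the figures above illustrate and do not predict.

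None of this touches the timing of collection. The schedule cannot be read as restarting after the second injection, because the only visits added for re-injected participants are at 7 or 9 months. A condensed article may leave injection-level tables to a fuller document, but the collection schedule it states is specific.

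**Conclusion.** The timing point holds without any assumption about treatment effect. Local reactions to a second injection are first asked about after 60 or 90 days, against about 30 days for the first. It concerns short-lived local reactions in the re-injected subset and does not affect the primary efficacy comparison.

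The denominator point holds conditionally. If treatment affects pain, so that placebo participants are re-injected more often, case counts per arm shrink a per-injection ratio by a factor of roughly 0.8 to 0.9. This rests on assumed re-injection shares and on FHSQ pain standing in for the actual trigger. A small excess could disappear; a large one would be diluted but still seen. A reader might also infer that late recall deepens this dilution. The arithmetic shows the opposite: the two problems partly offset each other in the ratio, while both lose information.

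The sections on outcome measurements and on adverse events need reconciling about months 7 and 9. If events are collected then, only re-injected participants are observed for longer. If they are not, safety follow-up after a second injection ends at month 6.

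**What to change.** 1. Add a dated local-reaction line (pain, effusion, heat, with grade) to the medication diary already returned monthly. This brings the report of a second-injection reaction to within about a month and links it to the injection by date.
2. Keep the per-arm counts. Beside them, report events from first injection to month 1, with the month-1 form completed before any day-30 injection so that everyone has had exactly one. Report second-injection events separately, with the number of injections given as denominator. The second-injection table is descriptive, because participants reach it by not improving and by not having had severe adverse effects.
3. State whether adverse events are collected at the 7- and 9-month visits, and make the two sections agree. If they are, show those events separately because only re-injected participants contribute. This step settles follow-up; it does not shorten recall.

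The cost is one diary line with slight participant burden, one extra table and a clarifying sentence. No visit, injection rule or sample size changes.

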### Sample size

The sample size for the study has been pre-specified using an *a priori *power analysis using the primary outcome measure of the pain domain of the FHSQ [42]. One hundred and forty two participants (i.e. 71 per group) will provide power of 90% to detect a minimally important difference in the pain domain of the FHSQ (i.e. 14 points on the FHSQ questionnaire) with the significance level set at p < 0.05. A difference of 14 points was determined to be a clinically significant difference worth detecting [43] and a standard deviation of 25 was derived from a previous report [44]. This calculation included a 5% drop-out rate [13]. However, we will aim to recruit 150 participants (~75 participants per intervention group). Further, we have conservatively ignored the extra precision provided by covariate analysis when estimating the sample size.

### Statistical analysis

Statistical analysis will be undertaken using SPSS version 14.0 (SPSS Corp, Chicago, Ill, USA) and STATA 8 (Stata Corp, College Station, Tex., USA) statistical software. All analyses will be conducted on an intention-to-treat principle using all randomised participants [45-47]. Missing data will be replaced with the last score carried forward [48]. Standard tests for normal distribution will be used and transformation carried out if required.

Demographic characteristics (gender, age, weight, height, body mass index) will be determined for the baseline visit for each treatment group. Summary statistics will be calculated for duration of symptoms, side affected (left, right, bilateral), grade of OA at the first MPJ [19] as well as all primary and secondary outcome measurements for each treatment group.

Analyses will be conducted on 1, 3 and 6 month outcome measures. The continuously-scored outcome measures at 1, 3 and 6 months will be compared using analysis of covariance with baseline scores and intervention group entered as independent variables [49,50]. The exception to this will be the plantar pressure measurements which will be analysed at baseline, 1, 3 and 6 months using two-way repeated measures analysis of variance statistics. Post-hoc comparisons will be performed using Bonferroni-adjusted t-tests. Nominal and ordinal scaled data will be compared at 1, 3 and 6 months using Mann-Whitney U-tests and chi-square analyses (or Fisher's exact test where appropriate) respectively. Effect sizes will be determined using Cohen's *d *(continuous scaled data) or odds ratios (nominal scaled data and ordinal scaled data) as appropriate.

The outcome measurements obtained at 7 or 9 months for participants that receive a second and final intra-articular injection (of Synvisc^® ^or sterile saline according to the treatment group they are in) on days 30 or 90 respectively, will also be analysed as described above. These analyses will be classified as secondary outcomes.

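### Carrying the last score forward as the fixed missing-data rule treats pre-injection scores as 6-month outcomes; the bias is small at the planned 5% dropout but grows, in either direction, if dropout differs by arm

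*Protocol article*

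**What the plan says.** The Statistical analysis section fixes the analysis set and the missing-data rule in consecutive sentences: "All analyses will be conducted on an intention-to-treat principle using all randomised participants", then "Missing data will be replaced with the last score carried forward". The rule is not limited to any outcome or visit. The analysis it feeds is stated in the same section: "The continuously-scored outcome measures at 1, 3 and 6 months will be compared using analysis of covariance with baseline scores and intervention group" as the independent variables.

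The section on primary outcome measures places measurements at "four time-points at baseline, 1, 3 and 6 months post-treatment". The Sample size section allows for 5% dropout overall and does not split it by arm. The Discussion expects the injection procedure itself to produce a large placebo response and cites a meta-analysis in knee osteoarthritis that attributes 79% of the efficacy of intra-articular hyaluronan to placebo.

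**The concern.** Carrying a score forward assumes that the participant would not have changed after the last attended visit. The protocol expects the opposite, since scores should move away from baseline in both arms. Someone lost before month 1 contributes a baseline score at all three time points. For that person the outcome and the covariate in the ANCOVA are the same number, and the filled-in value counts as a measurement with no added uncertainty.

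Two consequences follow for the pain and function subscales. With a true effect, each dropout pulls the contrast towards zero, even if dropout is equal. If dropout is unequal, the arm that loses more people looks worse than it is, because more of its members are held at a low early score. That can create a difference where none exists, in favour of either arm, so the rule cannot be defended as always conservative.

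A separate problem affects two secondary outcomes. Global satisfaction with treatment and self-reported symptom change have no pre-treatment score. For a participant lost before month 1 there is nothing to carry, so the rule and the commitment to analyse all randomised participants cannot both be met.

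**Working it through.** **The plan's own figure.** The Sample size section sets 90% power ("will provide power of 90% to detect a minimally important difference in the pain domain of the FHSQ"), the target difference ("A difference of 14 points was determined to be a clinically significant difference worth detecting"), the spread ("a standard deviation of 25 was derived from a previous report") and the test level ("with the significance level set at p < 0.05"). Two-sided, n per arm = 2 × (1.960 + 1.282)² × (25/14)² = 67.0. Dividing by 0.95 gives 70.5, so 71 per arm and 142 in total, as stated. (Rounding up to 68 before dividing gives 72 per arm, 144 in total.) The sample size is not in dispute and does not depend on the missing-data rule.

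**Inputs for the bias.**
- From the protocol: SD 25, 71 per arm, visits at 1, 3 and 6 months, 5% dropout.
- Assumed, because the documents give no figures: placebo improvement of 8, 14 and 18 points at 1, 3 and 6 months; a true difference D that is the same at every visit; baseline-to-follow-up correlation 0.5; half of dropouts lost before month 1, the rest all lost either just after month 1 or just after month 3; dropouts who would otherwise have changed like the rest of their arm. Improvement counts as positive.

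**Formula.** With dropout d in an arm, the expected month 6 change after carrying forward is (1 − d) × m6 + (d/2) × 0 + (d/2) × mL. Here m6 is the arm's true month 6 change and mL is its change at the later dropouts' last visit (month 1 or month 3).

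**Equal dropout, 5% per arm, D = 14, later half lost after month 1.**
- Active: 0.95 × 32 + 0.025 × 22 = 30.95.
- Placebo: 0.95 × 18 + 0.025 × 8 = 17.30.
- Difference: 13.65. It is also 13.65 if the later half leave after month 3 (31.10 − 17.45).

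**Unequal dropout within the planned 5% overall (2.5% versus 7.5%), D = 0.** Each dropout costs on average (18 + 10)/2 = 14 points, or (18 + 4)/2 = 11 points if the later half leave after month 3. The shift is 0.05 × 14 = 0.70 or 0.05 × 11 = 0.55 points against the arm with more dropout.

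**Hypothetical 5% versus 15%.** The first figure has the later half lost after month 1, the second after month 3.

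| True D | Placebo / active dropout | Expected estimate |
|---|---|---|
| 14 | 5% / 15% | 28.85 − 17.30 = 11.55; 29.30 − 17.45 = 11.85 |
| 14 | 15% / 5% | 30.95 − 15.90 = 15.05; 31.10 − 16.35 = 14.75 |
| 0 | 5% / 15% | 15.90 − 17.30 = −1.40; 16.35 − 17.45 = −1.10 |
| 0 | 15% / 5% | +1.40; +1.10 |

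**Error rate.** The baseline-adjusted standard error is 25 × √(1 − 0.5²) × √(2/71) = 3.63 points. A shift b under the null gives type I error 1 − Φ(1.96 − b/3.63) + Φ(−1.96 − b/3.63). This is 5.3% to 5.4% for b = 0.55 to 0.70, and 6.1% to 6.7% for b = 1.1 to 1.4.

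**Simulation check.** Simulating trials of 71 per arm under the same assumptions, 3,000 per scenario, gave 13.6 at 5%/5%, 11.6 to 11.8 at 5%/15% and 14.8 to 15.1 at 15%/5%. Null shifts at 5% versus 15% were 1.1 to 1.4 points. For the true 14-point effect, interval coverage was about 90% when active dropout was 15%. In the same runs a baseline-adjusted ANCOVA of observed month 6 scores recovered 13.9 to 14.1 for a true 14 with about 95% coverage. The shift therefore comes from the filling-in rule.

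**Range for the assumed placebo gain.** Suppose instead that every dropout leaves before month 1 and the placebo gain is g = 10, 20 or 30 points. Then the expected contrast is (1 − dA)(g + D) − (1 − dP)g, where dA and dP are active and placebo dropout. With D = 0 and all of a 5% overall dropout in one arm (0% versus 10%), the false difference is 1, 2 or 3 points. With 75 per arm and an unadjusted standard error of 25 × √(2/75) = 4.08, type I error is about 5.7%, 7.8% or 11.4%.

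**The case against.** The strongest reply is that the harm is small under the plan. At 5% dropout the shift is 0.35 points if dropout is equal and about 0.6 points with a threefold imbalance, against a standard error of about 3.6 and a target of 14. Nothing in the documents indicates that dropout will differ by arm. The optional second injection, open to non-improvers in both groups, also gives them a reason to stay. All of this stands, and it limits the size of the point.

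A reader might infer that participants who know their allocation will leave one arm more than the other. The Design section rules that premise out: participants and assessors are blinded, and only the injector is not. Unequal dropout could still arise through lack of relief or injection-site reactions, but that is a possibility and not something the protocol predicts. For a participant who truly would not have improved, the carried score is close to the missing one, so the error is smaller than in the figures above.

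A reader might also take 5% versus 15% as the expected case. It is 10% overall, twice the plan, and is shown only to indicate how the bias grows.

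It can also be said that an analysis plan not shown may add sensitivity analyses. That is fair, and their absence from the article is not criticised here. The article does, however, commit to the rule itself for all analyses. The problem with scales that lack a baseline is narrow: with 5% dropout and half of it early, 150 × 0.05 × 0.5 is about four participants, on secondary outcomes only.

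**Conclusion.** The point holds in a limited form. The protocol fixes a missing-data rule whose assumption conflicts with its own expectation of a large placebo response. The rule dilutes a true effect and can bias the contrast either way if dropout rate or timing differs by arm, even when dropout is random within arm.

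Under the stated assumptions the bias at the planned 5% is well below sampling error. It reaches about 1 to 1.5 points under the null, with type I error of about 6% to 7%, only in the hypothetical 5% versus 15% case, and it grows with the placebo improvement. The placebo trajectory, the correlation, the timing of dropout and the split by arm are all assumed. The documents do not support a claim that the trial's result will be materially distorted at the planned dropout. The change is still worth making, because the bias is avoidable and actual dropout is unknown until follow-up ends. For the satisfaction and symptom-change scales, the rule cannot be carried out for participants lost before month 1.

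**What to change.** Make the primary analysis of each continuous outcome now assigned to ANCOVA a likelihood-based mixed model for repeated measures on all observed post-baseline visits. Include baseline score, arm, visit, arm-by-visit and baseline-by-visit terms, and read the 1, 3 and 6 month contrasts from that model. Alternatively, keep the planned ANCOVAs and run them on multiply imputed data. Retain the last score carried forward only as a sensitivity analysis. State how participants lost before month 1 are handled for the satisfaction and symptom-change scales.

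The cost is revised analysis wording and a modest amount of extra analysis work. It needs no new data, visits or participants, and the sample size is unaffected. The change should be settled before treatment codes are broken.

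### Normality tests on the trial's own data decide whether the FHSQ primary outcomes are transformed, which can move the primary effect off the point scale on which the 14-point target and 142 participants were set

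*Protocol article*

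**What the plan says.** All from the protocol article.

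- **Transformation rule (Statistical analysis, first paragraph):** "Standard tests for normal distribution will be used and transformation carried out if required". It stands beside the intention-to-treat and missing-data rules that apply to every analysis. No outcome is exempted, and neither the test nor the transformation is named.
- **Model (Statistical analysis):** continuous outcomes at 1, 3 and 6 months "will be compared using analysis of covariance with baseline scores and intervention group entered as independent variables". Plantar pressures are the one exception.
- **Effect measure (Statistical analysis):** "Effect sizes will be determined using Cohen's" *d* for continuous data. This does not depend on the normality tests.
- **Summaries (Statistical analysis):** descriptive statistics are planned for symptom duration, side and grade, "as well as all primary and secondary outcome measurements for each treatment group".
- **Primary outcomes (Primary outcome measures):** the pain and function "subscales of the Foot Health Status Questionnaire (FHSQ").
- **Target (Sample size):** "A difference of 14 points was determined to be a clinically significant difference worth detecting"; "a standard deviation of 25 was derived from a previous report"; power 90% "with the significance level set at p < 0.05"; 71 per group, 142 in total, with 5% drop-out included.

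**The concern.** The trial asks whether hyaluronan beats saline by an amount that matters to patients, and the protocol sets that amount as 14 points on the FHSQ pain scale. The transformation rule lets a preliminary test on outcome data choose the scale of the primary analysis. If a transformation is applied, the model estimates a different quantity from the one the trial was sized on, and the result may fall on the other side of 0.05. Two primary outcomes at three visits give 2 × 3 = 6 primary comparisons, and nothing in the text requires the same scale for all six.

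The rule also guards against something that hardly matters here. ANCOVA does not need normally distributed scores, and with about 70 per group its test is robust to the skewness and boundedness expected of a questionnaire score.

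**Working it through.** **1. The scale on which the trial was sized.** Inputs from Sample size: difference 14, SD 25, alpha 0.05 (taken as two-sided), power 90%, drop-out 5%.

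n per group = 2 × [SD × (z₀.₉₇₅ + z₀.₉₀) / difference]² = 2 × [25 × (1.960 + 1.282) / 14]² = 67.01.

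With drop-out: 67.01 / 0.95 = 70.5, so 71 per group and 142 in total. This matches the stated figure exactly. A one-sided test would need only 55 per group before drop-out and does not match. The target therefore sits on the raw point scale.

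**2. What a transformation does to the target.** The protocol names no transformation, so the log is used only as an example. A 14-point gain is a ratio of (30 + 14)/30 = 1.47 from a score of 30, but (70 + 14)/70 = 1.20 from a score of 70. No single effect on the log scale corresponds to 14 points.

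**3. What Cohen's d does to the target.** The planned effect is d = 14/25 = 0.56, but only if the SD is 25. Over an assumed range of SDs:

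| SD (assumed) | d for 14 points | Points for d = 0.56 |
|---|---|---|
| 15 | 14/15 = 0.93 | 8.4 |
| 20 | 14/20 = 0.70 | 11.2 |
| 25 | 14/25 = 0.56 | 14.0 |
| 30 | 14/30 = 0.47 | 16.8 |

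So d can be turned back into points, but only through its SD.

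**4. Is transformation needed for validity?** Simulation: normal scores with SD 25 clipped to 0–100, baseline correlation 0.5, 71 per group, no treatment effect, 2,000 trials per setting. SD and group size come from the protocol. The 0–100 range, shape, means and correlation are assumptions.

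| Mean score | Shapiro-Wilk on scores rejects | Type I error, untransformed ANCOVA |
|---|---|---|
| 50 | 28% | 4.2% |
| 65 | 97% | 5.4% |
| 75 | 100% | 4.4% |

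A run of 4,000 trials per setting with scores rounded to steps of 6.25 points gave 4.9–5.4%. Smaller runs of 1,000 trials gave about 5–7%. The simulation standard error there is √(0.05 × 0.95 / 1,000) = 0.7 percentage points, so the top of that range is mostly noise, and the larger runs are the better guide.

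**5. How often would the rule fire?** This depends on what is tested.

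- On scores, the test rejected in 24–100% of unrounded or mixed settings, and in 76–100% when scores were rounded to steps of 6.25 or 8.33 points.
- On ANCOVA residuals, with steps of 6.25 points, it rejected in 5%, 12%, 25% and 74% of trials at means of 50, 60, 65 and 75. Across all settings tried, the range was 5–84%.

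**6. Can the choice change the conclusion?** Same assumptions, with a 10-point shift added before clipping, 1,000 trials per setting. ANCOVA on raw scores and on log(score + 1) disagreed on p < 0.05 in 11–22% of trials. Power was 73–78% raw and 61–66% log. These figures compare the two scales directly. They do not simulate the full test-then-transform procedure.

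**The case against.** The strongest case is that this is one routine sentence about checking assumptions in a condensed article. Transformation is conditional. If it is not done, the planned ANCOVA gives an adjusted difference in points. The choice of transformation, back-transformation and confidence intervals are details commonly left to an analysis plan, and their absence is no fault. The sentence also covers paracetamol grams, strength and plantar pressures, where a transformation may be sensible. Most of this stands, and the point does not rest on any missing detail. What it does not answer is that the rule is written down and, as written, includes the FHSQ primaries.

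Three stronger readings are tempting, and the documents do not support them.

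- **That the result could not be judged against 14 points at all.** This goes too far. The rule may not fire, d multiplied by its SD returns points, and group summaries are planned. Those summaries are a partial remedy: they are not described as baseline-adjusted differences with an interval.
- **That the normality tests also lead to Cohen's d.** They do not. It is planned for continuous data whatever the tests show, and the article never says it is the only result to be reported.
- **That the rule would fire nearly always.** This holds only if raw scores are tested and the scores are coarse or near their ceiling. With residuals, rejection can be as low as 5%. A significant test also need not lead to a transformation, since the wording leaves that to whether it is required.

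Nor has any inflation of type I error from the rule been shown. The harm demonstrated is a change of scale, a loss of power with the example transformation, and conclusions that can differ.

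**Conclusion.** The point holds in limited form. The protocol lets tests on trial data decide the scale of the primary analysis, while the target and sample size are fixed in raw FHSQ points. If a transformation is made, the direct link to 14 points is lost for the primary estimate. With a log as the example, the significance verdict differs from the raw analysis in 11–22% of trials under a 10-point shift. Untransformed ANCOVA at this size needs no such protection, since its error rate stays close to 5%.

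These sizes rest on assumed clipped-normal scores on a 0–100 range, a baseline correlation of 0.5 and a log transformation that the protocol does not name. The frequency of firing cannot be fixed from the document. The arithmetic of the sample size and the choice of ANCOVA are sound. This is a free or cheap improvement, not a flaw that undermines the trial.

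**What to change.** Add to Statistical analysis, in substance:

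1. FHSQ pain and function at 1, 3 and 6 months are analysed by ANCOVA on untransformed scores, whatever normality tests show.
2. The reported effect is the baseline-adjusted difference between groups in points with its 95% CI, read against 14 points for pain.

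A transformed analysis, or one with robust or bootstrap standard errors, can be kept as a sensitivity analysis, and Cohen's d as a supplement. The normality rule may stay for skewed secondary outcomes such as paracetamol use.

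The cost is about two sentences. No data collection changes, and the sample size stays at 142 because it was calculated on this scale.
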